### Trial design {8}

This is the protocol of a parallel-group, controlled, randomized trial, with a pre-post and repeated follow-up measures intergroup design. This trial is framed in the superiority framework.

A two-arm trial is going to be carried out. For this reason, a waiting list has been chosen as a comparator. Participants with low to moderate anxiety/depressive symptoms will be randomly assigned to Group 1: Unified Protocol for Transdiagnostic Treatment of Emotional Disorders (UP) intervention, or Group 2: Wait-List Control group.

The assessment will be conducted at three-time points for Group 1: an initial assessment before being randomized (pretreatment; T0), at the end of the intervention (post-treatment; T1), and 3 months after the completion of the intervention (T2). Group 2 will be assessed on T0 and T1. T2 would not be measured in this group since after T1 they will start treatment.

CONSORT patient’s flowchart is presented in Fig. 1.

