#### Intervention description {11a}

## Unified Protocol

The UP focuses on different strategies of emotion regulation to address neuroticism, a common factor in all emotional disorders (ED). This intervention intends to address dysfunctional emotional regulation strategies in participants and encourages the use of more adaptive strategies to promote tolerance to intense negative emotions. Participants will receive online, synchronous group therapy based on the UP model for 10 subsequent weeks, with a duration of 90 min for each meeting. After every session, they will receive the chapter of the UP’s Spanish patient’s workbook [6] with the notions addressed in the session and the indications to practice during the week.

Contents of each session:Session 1:

Coordinators’ and participants’ introductions. Session framework. Introduction to the approach and ED. Conceptualization of ED and identification of their own intense emotions, aversive reactions, and avoidance efforts.Session 2:

Module 1: Motivation for change and commitment to treatment. Describing issues, goals, and steps to accomplish them. Introduction to change motivation. Decision balance exercise.Session 3:

Module 2: Understanding emotions. Introduction to the topic of this session (psychoeducation of emotions). Presentation of the three-component model and introduction to the concept of Emotion-Driven Behaviors (EDBs), as well as the antecedents and consequences of emotional experiences.Session 4:

Module 3: Emotional awareness training. Introduction to mindfulness. Non-judgment emotional awareness exercises will be carried out during the session, and participants will receive afterwards by email with the taped audio so as to do it during the week. Introduction to emotional induction and practicing mindfulness when facing stimuli that trigger emotions (videos/audio). Introduction to anchoring in the present.Session 5:

Module 5: Cognitive flexibility. Introduction to cognitive flexibility. Ambiguous image exercise. Introduction to mind traps and cognitive re-evaluation exercise during the session.Session 6:

Module 5: Emotional avoidance and EDBs. Introduction to emotional behaviors. Introduction to EDBs and avoidance types. A cognitive suppression exercise will be carried out during the session. Working with alternative actions.Session 7:

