### Wait-List Control

Participants in the waiting list control will receive the same intervention as described above after the end of the group intervention. Participants on the waiting list will complete the same assessments as the intervention group (T0, T1), except the last one (T2).

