### Criteria for discontinuing or modifying allocated interventions {11b}

In this study, the criteria for discontinuing the intervention will be (1) participants who fail to attend two or more sessions, (2) participants who have current suicidal plans or acts, and (3) participants who request to withdraw from the trial.

Participants who have current suicidal plans or acts will be withdrawn from the trial and will receive individual care.

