### Relevant concomitant care permitted or prohibited during the trial {11d}

In this trial, participants who receive another psychological intervention during their participation in the study will be excluded. Psychopharmacological interventions are permitted with the regard that the dose dosage remains stable during the trial.

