### Outcomes {12}

#### Primary outcomes

In this study, participants are expected to show improvement in anxiety (BAI), and depression (BDI II) at post-treatment (T1) compared to pre-treatment (T0), and this result is expected to remain stable for 3 months (T2). In Wait-List Control, it is expected that there would not be a significant improvement in these variables at T1 compared to T0.

The clinical cut-off point for these scales in the Argentine population is 10 points. A cut-off score ≥ 10 in the BDI and BAI indicates clinical anxiety or depression (mild, moderate, or severe). A score ≤ 10 indicates that symptoms of anxiety or depression are not clinically relevant.

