### Adverse event reporting and harms {22}

In this study, no harm or adverse events are anticipated (a pilot study has been conducted previously). However, in case of any adverse events, psychotherapists will take appropriate actions to address them. Patients will be encouraged to express any discomfort associated with the intervention and will be provided with information on public places for consultation/treatment.

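### Excluding participants who receive other psychological treatment after randomisation can bias the T1 comparison in either direction and tends to favour the uncontrolled three-month durability claim

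*Protocol article*

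**What the plan says.** The rule stands in the protocol article under concomitant care {11d}: "participants who receive another psychological intervention during their participation in the study will be excluded". It is separate from the eligibility criteria {10}, which deal with current and past-year therapy at entry. It applies to both arms.

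The section on discontinuing or modifying interventions {11b} has its own list: "the criteria for discontinuing the intervention will be (1) participants who fail to attend two or more sessions", then suicidal plans or acts, then a request to withdraw. Other therapy is not on it.

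The Wait-List Control section says that "Participants in the waiting list control will receive the same intervention as described above after the end of the group intervention". Until T1 that arm receives no trial treatment. The UP arm receives "online, synchronous group therapy based on the UP model for 10 subsequent weeks" and is assessed again at T2, "3 months after the completion of the intervention (T2"). For the wait-list, Trial design {8} says: "T2 would not be measured in this group since after T1 they will start treatment". The primary outcomes section expects improvement at T1 and adds that "this result is expected to remain stable for 3 months (T2").

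The statistical methods {20a} name a mixed linear model (MANOVA) but no analysis population. Section {20c} imputes missing data by random forest and does not say whether excluded participants count as missing.

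**The concern.** Starting other therapy is something that happens after allocation and can be a consequence of it. A wait-list member who is getting worse has reason to look elsewhere, and so does a UP participant who is not responding or who relapses after the course. That link to symptoms is an inference, not a statement in the article, but it is a plausible one. If such people leave, those who remain in each arm are selected on how they are doing, and the arms may be selected differently. Two results are at stake: the between-group contrast on BDI-II and BAI at T1, and the claim that gains in the UP arm hold to T2, which has no control arm to show the selection.

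**Working it through.** **What the rule does.** Other therapy is absent from the list of reasons to stop the intervention, and wait-list members have no trial treatment to stop before T1. For that arm, the natural effect of the rule is to end assessment or to remove the person from the analysis. The article does not say which.

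**Inputs.** The article gives no rate of outside treatment, so there is no figure to reproduce. From Sample size {14}: planned effect 0.5 SD, 75 per arm evaluable, 90 per arm randomised. My assumptions: outcome SD 1 with higher scores worse; propensity to seek other care correlated r = 0.3 to 0.5 with severity; a fraction p with the highest propensity is excluded; two-sided alpha 0.05.

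**Formula.** The mean of those retained in an arm falls by s(p) = r × φ(z) / (1 − p), where z is the (1 − p) normal quantile.

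| p | φ(z)/(1 − p) | s at r = 0.3 | s at r = 0.5 |
|---|---|---|---|
| 0.01 | 0.027 | 0.008 | 0.013 |
| 0.03 | 0.070 | 0.021 | 0.035 |
| 0.05 | 0.109 | 0.033 | 0.054 |
| 0.10 | 0.195 | 0.058 | 0.097 |
| 0.15 | 0.274 | 0.082 | 0.137 |
| 0.20 | 0.350 | 0.105 | 0.175 |

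**T1 contrast.** Estimated benefit = true benefit − s(wait-list) + s(UP).

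| Excluded, wait-list v UP | r | Shift in UP benefit (SD) |
|---|---|---|
| 10% v 10% | 0.5 | 0 |
| 3% v 1% | 0.5 | 0.013 − 0.035 = −0.02 |
| 10% v 5% | 0.3 | 0.033 − 0.058 = −0.03 |
| 15% v 5% | 0.5 | 0.054 − 0.137 = −0.08 |
| 20% v 0% | 0.5 | −0.17 |
| 5% v 15% | 0.5 | +0.08 |
| 0% v 10% | 0.5 | +0.10 |

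Simulation with 2,000,000 per arm agrees. With 15% v 5% and r = 0.5, a true 0.50 appears as 0.42; with r = 0 it stays at 0.50. Under a true difference of zero and 90 randomised per arm, the two-sided rejection rate rises from 0.05 to 0.12 at 20% v 5% (in favour of the wait-list), and to 0.085 at 5% v 15% (in favour of UP), both at r = 0.5.

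**Power in the 15% v 5% case.** If exclusions come off 90 per arm and are the only losses, power is about 0.78, against 0.92 with everyone kept. If they come off 75 per arm, it is about 0.70, against 0.86.

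**T2, UP arm only.** The rule runs for the 10-week course plus 3 months, and I take exclusion to depend on T2 severity. At r = 0.5 and 10 to 15% excluded, the T2 mean looks 0.097 to 0.137 SD better than that of the full arm. For change within those retained, with an assumed T1–T2 correlation of 0.6, multiply by (1 − 0.6): 0.039 to 0.055 SD. A true relapse of 0.20 SD would then show as about 0.16 to 0.15 SD within those retained, or about 0.10 to 0.06 SD against the full-arm T1 mean. Which comparison applies depends on whether the T1 scores of people excluded later stay in.

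**Imputation.** A forest trained on those who remain can use an excluded person's earlier scores. It still predicts the later score as if that person had behaved like someone with the same history who did not seek care.

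**The case against.** The strongest reply is that the article never says excluded *from the analysis*. The sentence sits under concomitant care, no section restricts the analysis to those who remain, and imputation is compatible with analysing everyone. Analysis sets are also commonly left to a SAP. This stands in part: a reader might infer that the plan removes these people from the analysis, and the text does not establish that. But a SAP cannot restore T1 or T2 scores that were never collected because the person had left.

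It is also fair that outside treatment may be rare. Entrants have had no psychological treatment for a year, the background section describes access as difficult, and the wait-list is promised the intervention. At 3% v 1% the T1 shift is only 0.02 SD.

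Four stronger readings are tempting and are not supported:

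- That the rule contradicts the harms section {22}, under which participants "will be provided with information on public places for consultation/treatment". The two can coexist. There is a tension, because acting on the information may trigger exclusion.
- That unequal exposure to the rule biases T1. Up to T1 both arms face the same window; the longer UP window matters only for T2.
- That a medication change leads to exclusion. The section asks for a stable dose but attaches no exclusion to a change.
- That other therapy goes unrecorded after baseline. A condensed article may simply omit such forms, and the schedule figure is not shown.

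**Conclusion.** The point holds as a badly fixed post-randomisation rule. If it is followed, the T1 contrast can move in either direction, by about 0.02 to 0.17 SD under the assumed rates and correlations, and by about nothing if both arms lose similar people at equal rates. A reader might infer that it inflates the UP effect. The documents do not support a direction: if the wait-list loses more people who are doing badly, the UP effect is understated. A reader might also take power of 0.70 as the consequence, but that figure removes people from a 75 per arm that is already net of dropout; from 90 it is about 0.78.

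The T2 effect has a clearer direction. It favours stability whenever those doing worse seek care, by about 0.04 to 0.06 SD in within-person change or 0.10 to 0.14 SD against the full-arm T1 mean, at 10 to 15% excluded, r = 0.5 and a T1–T2 correlation of 0.6. All of these sizes are illustrative, since the article gives no rate of outside treatment.

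**What to change.** In {11d}, replace the exclusion with wording to this effect: participants who start another psychological treatment after randomisation are still assessed at T1, and at T2 in the UP arm, and are analysed in the arm to which they were randomised. Report receipt of other psychological treatment by arm. Treat any analysis without these participants as supportive only.

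Whether they may continue in the group sessions is for the investigators, who should reconcile sections {11b}, {11d} and {22}.

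The cost is an amendment through the ethics committee, as {25} provides, and continued contact with a few participants. Recruitment began in April 2022, so the change cannot recover assessments already missed. The downside is that the estimate becomes UP versus waiting list including any outside care, which may be slightly smaller than an effect free of other treatment.

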### Provisions for post-trial care {30}

No potential harm is expected from this study.

### Outcomes {12}

#### Primary outcomes

In this study, participants are expected to show improvement in anxiety (BAI), and depression (BDI II) at post-treatment (T1) compared to pre-treatment (T0), and this result is expected to remain stable for 3 months (T2). In Wait-List Control, it is expected that there would not be a significant improvement in these variables at T1 compared to T0.

The clinical cut-off point for these scales in the Argentine population is 10 points. A cut-off score ≥ 10 in the BDI and BAI indicates clinical anxiety or depression (mild, moderate, or severe). A score ≤ 10 indicates that symptoms of anxiety or depression are not clinically relevant.

#### Secondary outcomes

Participants are expected to show improvement in emotion regulation (DERS), quality of life (MQLI), positive and negative affect (PANAS), and hopelessness (BHS) at post-treatment (T1) compared to pre-treatment (T0), and this result is expected to remain stable for 3 months (T2). No significant changes in Wait-List Control on these variables are expected at T1 compared to T0.

#### Participant timeline {13}

The schedule of enrolment, interventions, and assessments are shown in Fig. 2.

**Fig. 2 Fig2:**
[figure not shown]
Schedule of enrolment, interventions, and assessments

#### Sample size {14}

The sample size has been estimated based on a meta-analysis of previous studies of the application of the Unified Protocol in emotional disorders compared to a control group [21]. These studies showed a medium effect size (0.45 g* hedges*) on post-treatment measures. A median effect size (0.5) was assumed to detect differences between the intervention and the control group. G*Power software was used to calculate the sample size. For two groups, with a statistical power of 0.80, and an alpha of 0.05, it is estimated that a total of 150 participants will be required (75 for each condition). Given that previous studies have reported a dropout rate between 15 and 20% [22], the total sample required will be 180 participants, 90 for each group.

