## Assignment of interventions: allocation

### Sequence generation {16a}

Simple randomization will be used in this study. Participants who met the inclusion criteria will be randomized to either treatment condition (UP) or Wait-List Control, using specific online software (https://www.randomizer.org/). Ratio allocation will be 1:1 (approximately).

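### The sample-size total of 150 does not follow from its stated inputs, and 180 randomised keeps 150 evaluable only up to 16.7% dropout within the stated 15 to 20% range

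*Protocol article*

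**What the plan says.** Everything is in the protocol article, section Sample size {14}. The calculation starts from a meta-analysis of Unified Protocol studies against control: "These studies showed a medium effect size (0.45 g* hedges*) on post-treatment measures". It then fixes the design value: "A median effect size (0.5) was assumed to detect differences between the intervention and the control group". The remaining inputs are two groups "with a statistical power of 0.80, and an alpha of 0.05", with G*Power as the software. The result is that "it is estimated that a total of 150 participants will be required (75 for each condition"). Dropout is then allowed for: "previous studies have reported a dropout rate between 15 and 20% [22], the total sample required will be 180 participants", that is, 90 per arm. Section Sequence generation {16a} adds "Ratio allocation will be 1:1 (approximately").

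The section names neither the G*Power test nor whether alpha is one- or two-sided. Section Statistical methods {20a} plans a mixed linear model, also labelled MANOVA, with a Bonferroni-Holm correction.

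**The concern.** The section prints a complete set of inputs and a result, and the two disagree. Three effect sizes are in play: 0.45 from the source, 0.5 as the assumption, and the value that 75 per arm actually corresponds to, which is neither. The step from 150 to 180 also looks as if it falls short over part of the dropout range it is meant to cover.

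This section is the only justification given for randomising 180 people. If the trial gives a null or borderline result, readers will come here to learn which effect it could have detected, and the printed figures would mislead them in both directions: 150 is more than 0.5 requires and less than 0.45 requires.

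**Working it through.** **Inputs from Sample size {14}:** assumed effect 0.5; cited effect 0.45; power 0.80; alpha 0.05; 150 evaluable (75 per arm); dropout 15 to 20%; 180 randomised (90 per arm). Allocation of about 1:1 is from Sequence generation {16a}. **My assumption:** a two-sample t-test, two-sided unless noted.

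**Step 1. Trying to reproduce 150.** The normal approximation is n per arm = 2(z₁₋α/₂ + z₁₋β)²/d², with z values 1.960 and 0.842.

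- d = 0.5: 2 × (2.802)²/0.25 = 62.8, so 63 per arm. The exact noncentral-t solution is 63.8, so 64 per arm and **128 in total**.
- d = 0.45: 2 × (2.802)²/0.2025 = 77.5, so 78 per arm. The exact solution is 78.5, so 79 per arm and **158 in total**.
- One-sided alpha 0.05, exact: 51 per arm (102) at 0.5 and 62 per arm (124) at 0.45.
- Solving the exact two-sided formula for d at 75 per arm and 80% power gives **d = 0.460**.

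So 150 follows from neither effect size, one-sided or two-sided.

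**Step 2. Could another procedure explain it?** Totals at an effect of 0.5:

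| Route | Total |
|---|---|
| Alpha halved to 0.025 | 156 |
| Power raised to 0.85 | 146 |
| Two-outcome MANOVA, f² = 0.0625 | 158 |
| Repeated-measures between-groups test, 2 or 3 times, assumed correlation 0.5 | 98 or 86 |
| Wilcoxon-Mann-Whitney at minimum relative efficiency 0.864 | 148 |
| 128 already inflated for 15% dropout, 128/0.85 | 151 |

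Some come close, but none gives 150. The first two change a stated input. The Wilcoxon route is not the planned analysis. The last would count dropout twice once 150 is inflated to 180.

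**Step 3. Dropout.** Evaluable = 180 × (1 − dropout).

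- At 15%: 180 × 0.85 = 153.
- At 20%: 180 × 0.80 = 144.
- Break-even: 1 − 150/180 = 16.7%.
- Randomised number needed to keep 150: 150/0.85 = 176.5, so 177; 150/0.80 = 187.5, so 188.

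**Step 4. Power delivered.** Exact two-sided t-test at alpha 0.05, with noncentrality d√(n/2) and n per arm. For 72 per arm, for example, this is 0.5 × √36 = 3.00 and 0.45 × √36 = 2.70.

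| Evaluable (per arm) | Power at 0.5 | Power at 0.45 |
|---|---|---|
| 153 (76.5) | 0.867 | 0.790 |
| 150 (75) | 0.860 | 0.782 |
| 144 (72) | 0.846 | 0.765 |

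The 0.765 is 0.7648 before rounding, hence 76% as a whole number. With 72 per arm, 80% power is reached at d = 0.470.

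**The case against.** The strongest reply is that the error is on the safe side. The section assumes one design effect, 0.5, and at that effect the stated 80% power is exceeded across the whole dropout range. This stands. A reader might infer that the trial is undersized; the document does not support that at its own assumption.

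A reader might also infer that the plan fails a promise of 80% power at 0.45. It makes no such promise. The 0.45 is reported as background, and choosing 0.5 after disclosing it is a planning judgement made in the open, although no reason is given for expecting more than the source found. The gap is also modest, 76 to 79% against 80%, and depends on the analysis. If baseline were used as a covariate with a pre-post correlation of 0.3 to 0.5 (an assumption; the document gives none), 72 per arm would give about 80 to 87% power at 0.45. Clustering from group delivery and the Holm correction push the other way. Neither direction is settled.

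On dropout, it is tempting to say that 180 fails at the stated rate. The stated rate is a range, and at its lower end 180 is enough (177 needed). That 180 came from 150 × 1.20 is plausible but is an inference; 177 rounded up fits as well.

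Finally, a condensed article may leave the test and sidedness to the full protocol, so 128 and 158 are conditional figures. That is fair, but it does not rescue 150: the disagreement is between printed inputs and a printed result, and it holds under either sidedness of the standard calculation.

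**Conclusion.** The point holds, at moderate severity. The total is not reproducible from its stated inputs: 150 lies 22 above the 128 needed at 0.5 and 8 below the 158 needed at 0.45. The dropout allowance is short only above 16.7%, by at most 6 evaluable participants (150 − 144) at the 20% end.

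All power figures assume a two-sided two-sample t-test on post-treatment scores at alpha 0.05, before clustering, multiplicity or baseline adjustment. What is established is a misreported calculation, with ample power at the assumed effect and slightly under 80% at the cited one on that test. It is not established that the trial is underpowered or that more participants are needed.

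**What to change.** Keep 180 and replace the calculation in Sample size {14} with what that number delivers, for example:

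*180 randomised leaves 153 to 144 evaluable at 15 to 20% dropout; 144 gives 85% power for d = 0.5, 76% for 0.45 and 80% for d = 0.47 (two-sided alpha 0.05, two-sample t-test, before clustering, multiplicity and any baseline adjustment).*

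If a different G*Power procedure produced 150, name it and list its inputs, including sidedness, so that the figure can be reproduced. In that case the dropout sentence still needs correcting, because 180 does not keep 150 above 16.7% dropout.

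The cost is rewording only, with no extra patients. The sponsor has to state openly that power at the effect its own source reports is slightly below 80% on the simple test.
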